#### HSRC website

2.4.3

In addition to HSRC programming, all schools will receive access to the HSRC website^1^, which provides the research evidence for each program and shows the alignment of each program with Texas Essential Knowledge and Skills – curriculum standards for public schools in Texas. The website also provides step-by-step instructions on how to get recognized as a HSRC, a list of recognized schools, details on programs for different age groups, and resources. Resources include material such as physical activity guidelines, nutrition facts, mental health resources and positive youth development websites.

#### School recruitment

2.4.4

We will work with Texas A&M AgriLife Extension agents to identify schools that may be interested in participating in the study. Specifically, schools that have previously participated in AgriLife’s physical activity or nutrition programs in the past, or that have recently expressed interest in receiving school-based health programs, will be contacted. We will also share information about HSRC with eligible schools via email, at school health conferences, or at events where school staff are present. Schools that agree to participate will sign a memorandum of understanding and a site authorization that permits the conduct of research on the school campus. Schools will also complete an application for the HSRC initiative. The application lists the initial AgriLife programs that schools can choose to complete during the next year; however, schools can change their programs at any point throughout the school year.

#### Participant recruitment

2.4.5

We aim to recruit about 20 parents (320 total), 20 students (320 total), and 10 HSRC implementers (160 total) at each school (two cohorts of *n* = 8 schools) enrolled in the study. We will share recruiting materials online (e.g., email) and in-person (e.g., back-to-school events, student drop-off and pickup) to provide details about the study. Parents agreeing to participate will complete the consent form for their child and themselves, a short survey at pre- and post-intervention, and they will be compensated with a $10 gift card at each time point. The research team will meet in-person with children who have received signed parental consent to explain the study and answer any questions. Children will sign an assent form before participating in a survey and biometrics assessment at pre- and post-intervention. They will also receive an item worth $10–$15 (e.g., t-shirt, water bottle, active toy) for each data collection timepoint (pre- and post-intervention). Children who do not agree to participate in the study will still be allowed to participate in HSRC programs. HSRC implementers (e.g., Extension agents, school staff, administrators) will complete a consent form agreeing to participate, a survey pre- and post-intervention, and interviews following the intervention. They will be compensated with a $20 gift card for each survey and $50 for the interview.

#### Randomization

2.4.6

In each of the two cohorts, schools will be randomized to one of eight experimental conditions and will receive a different combination of implementation strategies (Table 2). In each school year, four schools will receive each implementation strategy, and four schools will not (all schools will receive the website as a constant implementation strategy). Schools and data collectors will be blinded to randomized conditions until a school completes data collection. An interim analysis (following processes outlined below) will be conducted between the two cohorts to determine if implementation strategies should be removed and/or replaced, as well as if any of the current implementation strategies should be modified.

**Table 2 tab2:** Randomized experimental conditions for this study.

Experimental condition	Constant	Factor 1	Factor 2	Factor 3
1	Website/TEKS alignment	None	None	None
2	Website/TEKS alignment	None	None	Enhanced engagement opportunities
3	Website/TEKS alignment	None	School-to-school mentoring	None
4	Website/TEKS alignment	None	School-to-school mentoring	Enhanced engagement opportunities
5	Website/TEKS alignment	Additional resources	None	None
6	Website/TEKS alignment	Additional resources	None	Enhanced engagement opportunities
7	Website/TEKS alignment	Additional resources	School-to-school mentoring	None
8	Website/TEKS alignment	Additional resources	School-to-school mentoring	Enhanced engagement opportunities

Each of the 8 conditions will be randomized one time per cohort.

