##### School-to-school mentoring

2.4.7.2

We define the school-to-school mentoring strategy as the research team facilitating connections between schools that are implementing HSRC at the same time as one another to provide a support system and technical assistance to improve implementation outcomes (i.e., acceptability, appropriateness, feasibility) – a recommendation based on qualitative interviews and focus groups. The main components of this strategy will be: (1) an introductory email, (2) monthly meetings, (3) a private Facebook group, and (4) quarterly newsletters. Immediately following randomization, participating schools will receive an introductory email welcoming them to the school-to-school mentoring program and informing them about its components (e.g., the Facebook group, newsletters). Starting around November (1–2 months into the implementation process), the research team will host monthly virtual meetings with implementers to discuss the programs being completed and successes and barriers to program implementation. At the first meeting, implementers will be invited to join a private Facebook group, which will serve as a hub for HSRC program implementers to discuss ideas, share insights on their implementation process, and seek advice outside of the group meetings. Within the Facebook group, the research team will post prompts periodically to foster engagement with the page. Finally, schools will receive quarterly newsletters designed by the research team (up to four times during the year), which will include the following elements: (1) a previously recognized HSRC school, (2) links to helpful resources for program implementation, (3) a spotlighted HSRC program, (4) a calendar of local county health-focused events, and (5) information on AgriLife Extension and its agents.

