### Outcomes

2.5

Baseline data collection (T1) will occur prior to randomization within the first 3 months of the academic year (Aug. 1 – Oct. 31). Post-test data collection (T2) will occur in the last 2 months of the academic year (April 1 – May 31). Data collection for parents and implementers consists of a survey, whereas data collection for students includes a survey and biometrics assessment. Parent and implementer surveys will be administered online via REDCap (an online survey platform), whereas student surveys and biometrics (i.e., objective measures of cardiovascular disease risk) will be collected during an in-person data collection event. A summary of constructs measured is included in Table 3.

**Table 3 tab3:** Summary of constructs measured.

Construct	Implementers	Students	Parents
Implementation outcomes			
Reach	P		
Dose delivered	P		
Acceptability, appropriateness, feasibility	O		
School characteristics	O		
Perceptions of healthy school recognized campus	O		
Effectiveness outcomes			
Metabolic syndrome		P	
Cardiovascular fitness		P	
Dermal carotenoids		P	
Body mass index		P	
Psychosocial determinants of physical activity and healthy eating		O	
Physical activity	O	O	O
Frequency of foods consumed	O	O	O
Engagement in the school and community		O	O
Sociodemographic characteristics	O	O	O

P, primary; O, other.

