#### Statistical and power analysis

2.6.1

This is an optimization study to screen and refine components of a support strategy for the HSRC initiative in preparation for a fully powered randomized controlled trial; thus, this study is not fully powered to examine differences in implementation or effectiveness outcomes (60). To analyze outcomes, we will use univariate and bivariate statistics to determine the distribution of outcome measures and to identify relevant covariates (61). To test between-implementation strategy differences on implementation and effectiveness outcomes, students at schools with and without each implementation strategy (independent variable) will be evaluated using a generalized linear model framework. Baseline scores will be added as a covariate (when applicable), post-intervention score is the outcome, and school is a clustering variable (62). Other covariates (e.g., school size), identified in the preliminary bivariate analyses, will also be included in the model. If missing data occurs, we will mitigate potential biases by analyzing multiple imputed datasets under an intention-to-treat approach (63). Analyses will be compared to per-protocol analyses (64). Interaction effects between strategies are normally small in behavioral trials; however, we will review plots of combinations of strategies to determine if a specific combination of strategies warrants further evaluation. If so, we will add an interaction term to our model. We will calculate standardized effect estimates for each strategy (i.e., Cohen’s *d*), compare effect estimates to make decisions about which components to include in the final support strategy, and report these estimates in our results.

As the goal of this project is to refine and optimize implementation strategies for testing in a future trial, we will conduct an interim analysis following the first cohort of schools using the approach outlined above. This analysis will be repeated following the second cohort of schools. Depending on the results of the interim analysis and potential changes to the strategies that result from the interim analysis, we will conduct a pooled analysis across both cohorts, unless the implementation strategies undergo substantive modifications between cohorts, in which case we will only report the individual results from each cohort.

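### Masking ends school by school in a design that uses each condition once per cohort, so conditions may be known or narrowed down before a cohort's measurements are complete

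*Protocol article*

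**What the plan says.** Protocol article, section 2.4.6 (Randomization), sets two rules. On allocation, the Table 2 footnote states "Each of the 8 conditions will be randomized one time per cohort", and the text gives the balance per factor: "In each school year, four schools will receive each implementation strategy, and four schools will not". On masking, it states "Schools and data collectors will be blinded to randomized conditions until a school completes data collection".

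Section 2.5 (Outcomes) gives the timing: "Baseline data collection (T1) will occur prior to randomization within the first 3 months of the academic year (Aug. 1 – Oct. 31") and "Post-test data collection (T2) will occur in the last 2 months of the academic year (April 1 – May 31"). It does not say whether randomization is one event after all eight baselines or follows each school's own baseline.

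Section 2.4.7.2 (School-to-school mentoring) adds that "Immediately following randomization, participating schools will receive an introductory email welcoming them to the school-to-school mentoring program". It also places the first mentoring meetings around November and counts that as one to two months into implementation.

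**The concern.** With eight schools and eight conditions drawn without replacement, each condition that becomes known shortens the list for the remaining schools. Release tied to a single school, rather than to the cohort, therefore passes on information about schools still to be visited.

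Two things are at stake.

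- **Before baseline.** Section 2.4.5 recruits volunteers, partly in person: "We aim to recruit about 20 parents (320 total), 20 students (320 total), and 10 HSRC implementers (160 total) at each school". If staff can anticipate a school's condition, who enrols and how measurements are taken could differ by condition. Randomizing after T1 is meant to rule this out.
- **At post-test.** The shuttle run in section 2.5.3.2 depends on effort and is led by a member of the research team. A collector who knows or suspects the condition may encourage children differently without intending to.

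Each factor contrast at the interim analysis compares four schools with four, and that analysis informs whether strategies are removed, replaced or modified (2.4.6, 2.6.1). A disturbance at a few schools would carry weight.

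**Working it through.** **Reproducing the plan's figure.** Table 2 lists the 2 × 2 × 2 = 8 combinations. Each strategy is on in 4 and off in 4, as section 2.4.6 states.

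**Which data collection ends masking?** Two meanings are possible.

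- *T1.* For schools this is the only workable meaning: mentoring schools are told at once after randomization (2.4.7.2), and strategies run during the year, so schools cannot stay masked to T2. The same sentence covers data collectors. On this meaning their masking has ended for every school by April, however the schools were randomized.
- *T2, for collectors only.* Masking then ends one school at a time between April 1 and May 31, while other schools are still to be measured.

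**Predictability under school-by-school release.** Assume every earlier school's condition is known when school k is reached, with n = 9 − k conditions left.

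- Full condition: the best guess is right with probability 1/(9 − k).
- One strategy: if a of the n remaining conditions have it on, the best guess is right with probability max(a, n − a)/n. This is averaged over P(a) = C(4,a)·C(4,n−a)/C(8,n).

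Example, school 3 (n = 6): a = 3 has probability 16/28, and a = 2 or 4 together 12/28. The result is 16/28 × 1/2 + 12/28 × 4/6 = 16/28 = 0.571.

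| School in order | Full condition | One strategy, best guess right | Given strategy already certain | At least one of three certain |
|---|---|---|---|---|
| 1 | 1/8 | 0.500 | 0 | 0 |
| 2 | 1/7 | 0.571 | 0 | 0 |
| 3 | 1/6 | 0.571 | 0 | 0 |
| 4 | 1/5 | 0.629 | 0 | 0 |
| 5 | 1/4 | 0.629 | 0.029 | 0.086 |
| 6 | 1/3 | 0.714 | 0.143 | 0.429 |
| 7 | 1/2 | 0.714 | 0.429 | 0.857 |
| 8 | 1 | 1.000 | 1.000 | 1.000 |

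Expected correct guesses for one strategy are the sum of the third column, 5.33 of 8, against 4 if nothing is known. The closed form agrees: 4 + 2⁷/C(8,4) − 1/2 = 4 + 128/70 − 0.5 = 5.33. For the full condition the sum is 2.72, against 1.0 if assignments were independent. The fourth column sums to 1.6 schools per strategy.

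The table applies to T1 visits if release follows each school's T1, and to T2 visits if it follows each school's T2.

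**Under joint release after the last T1.** No condition is known at any baseline visit. The best guess stays at 1/2 per strategy and 1/8 for the full condition at every school.

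**The case against.** The strongest reply is that section 2.5 puts T1 before randomization. Read as one phase followed by one randomization, no assignment exists during any baseline visit and nothing can be deduced. Joint mentoring meetings from around November, after T1 closes, fit that reading. The masking sentence may also mean only that a school does not learn its own condition until its own data are in; it does not say that one school's condition is passed to another. Release mechanics are, besides, something a journal article often leaves to the full protocol.

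Much of this stands. A reader might infer that later schools' assignments are in fact deducible before recruitment. The article does not support that as a fact: the T1 harm is conditional on school-by-school release. Certainty about the full condition arises only for the eighth school, and schools 2 to 4 are only weakly predictable.

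A reader might also turn the hit rates into a bias. If an anticipated condition shifted a school's result by δ between expected on and expected off, the raw contrast would move by δ/8 × (5.33 − 2.67) = 0.33δ. But δ is not in the documents, and section 2.6.1 adjusts for baseline scores where applicable. Adjustment would remove part of a stable difference in who enrolled. If extra effort occurred only at T1, it would push the estimate the other way. The figure is not the bias of the planned analysis.

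Two things remain. The article chose to state when masking ends, and tied it to one school and to data collectors by name; that is a stated rule, not an omitted detail. Section 2.5 does not settle the order, and counting November as one to two months into implementation makes a start before the last T1 plausible, though it does not prove that strategies are released then.

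**Conclusion.** The masking rule is badly fixed for a design with one school per condition in each cohort. On either meaning it fails to protect the whole cohort's post-tests: collectors are no longer masked at T2 (T1 meaning), or can narrow down the conditions of schools visited late (T2 meaning).

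Predictability before baseline is a further consequence only if data collection means T1 and release is school by school. It then amounts to 5.33 expected correct guesses of 8 per strategy against 4, rising from 0.50 at the first school to 0.71 at the seventh and certainty at the eighth. This assumes that each earlier condition is known to those visiting the next school. It is nil if all eight are randomized or released together after the last T1.

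The size of any resulting bias cannot be given from the documents. Baseline adjustment limits it for the health scores but not for dose delivered (2.5.1), which describes delivery during the year and has no natural baseline. The article itself says that "this study is not fully powered to examine differences in implementation or effectiveness outcomes". That does not remove the point, because the effect estimates still guide which strategies are kept.

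**What to change.** In section 2.4.6, replace the school-level trigger with a cohort-level one, for example: *All eight assignments of a cohort are drawn in one step and released to the schools together, after the last school of that cohort has completed T1 recruitment and measurement. Data collectors are told no school's condition until the last school of the cohort has completed T2.* Align the sentence on T1 and randomization in section 2.5, so that it says randomization follows the last baseline of the cohort.

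This is a cheap improvement in wording. If the trial already works this way, the text simply comes to match practice. The cost is that schools finishing T1 early wait for the last school before strategies are released. The T1 window closes on October 31 and mentoring meetings start around November, and scheduling the eight baseline visits close together would shorten the wait.

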#### Implementation support strategies

2.4.7

We selected and developed implementation strategies based on preliminary reports of barriers and facilitators to the use of the HSRC initiative (29, 35). The developed strategies are described below using Proctor’s recommendations to name, define, and specify implementation strategies when they are reported, as well as aligned with the StaRI reporting guidelines (36, 37). We also developed a Multiphase Optimization STrategy (MOST) logic model describing the randomized strategies’ hypothesized impact on implementation, behavioral, and health outcomes (Figure 1) (26, 38).

**Figure 1 fig1:**
[figure not shown]
MOST logic model.

##### Additional resources

2.4.7.1

We define the additional resources strategy as monetary support for participant incentives that could aid in improving program implementation outcomes (i.e., acceptability, feasibility). The research team will provide each Extension agent randomized to this strategy with a $2,000 budget to spend on incentives for student and adult participants in their HSRC programs – an amount based on our prior research. To streamline the process and provide example incentives for programs within HSRC – which was a recommendation from implementers – a password-protected page hosted on the HSRC website will feature an interactive form with some example incentive items and their estimated prices. Extension agents will work with their schools, access this page to view the items and complete an order request form for the items they would like. The research team then will reach out to confirm items, quantity, shipping address, total price, and estimated delivery date. Extension agents will be able to spend the $2,000 all at one time or spread out over the course of the year. They are also able to buy incentives beyond those included on the website, if they remain within their budget.

##### School-to-school mentoring

2.4.7.2

We define the school-to-school mentoring strategy as the research team facilitating connections between schools that are implementing HSRC at the same time as one another to provide a support system and technical assistance to improve implementation outcomes (i.e., acceptability, appropriateness, feasibility) – a recommendation based on qualitative interviews and focus groups. The main components of this strategy will be: (1) an introductory email, (2) monthly meetings, (3) a private Facebook group, and (4) quarterly newsletters. Immediately following randomization, participating schools will receive an introductory email welcoming them to the school-to-school mentoring program and informing them about its components (e.g., the Facebook group, newsletters). Starting around November (1–2 months into the implementation process), the research team will host monthly virtual meetings with implementers to discuss the programs being completed and successes and barriers to program implementation. At the first meeting, implementers will be invited to join a private Facebook group, which will serve as a hub for HSRC program implementers to discuss ideas, share insights on their implementation process, and seek advice outside of the group meetings. Within the Facebook group, the research team will post prompts periodically to foster engagement with the page. Finally, schools will receive quarterly newsletters designed by the research team (up to four times during the year), which will include the following elements: (1) a previously recognized HSRC school, (2) links to helpful resources for program implementation, (3) a spotlighted HSRC program, (4) a calendar of local county health-focused events, and (5) information on AgriLife Extension and its agents.

##### Enhanced engagement opportunities

2.4.7.3

We define enhanced engagement opportunities as physical activity and nutrition competitions encouraging schools and students to be active participants in HSRC programs to improve implementation outcomes (i.e., acceptability and appropriateness) – a strategy based on qualitative interviews and focus groups. More specifically, the two competitions were the “Walk Across Texas Mileage & Participation Contest” – aligned with the required Walk Across Texas program – and the “MyPlate Recipe Contest” – aligned with various nutrition programs within the HSRC initiative (e.g., Learn, Grow, Eat, and Go). For the Walk Across Texas Mileage & Participation Contest, students and school staff work toward two goals: (1) attain 10% adult participation in their Walk Across Texas event and (2) collectively accumulate an average of 26.2 walking miles per person – goals selected based on previous participation levels in HSRC programs. For each goal that schools meet, they earn a prize picked by the school’s principal (e.g., extra recess, no uniforms for a day). For the MyPlate Recipe Contest, students compete against one another and against other schools by crafting healthy, MyPlate-aligned recipes (e.g., use half-fruits and vegetables). Submissions will be evaluated for their nutritional value and creativity, and student winners will be awarded monetary prizes at each grade level. Additionally, the school with the highest percentage of student participation receives $500.

